### Data analysis plan

For all analyses, an ITT approach is used, where all study participants are included in analyses. For H1 and H2, comparisons of survival curves for each group are performed using SAS PROC PHREG and PROC GLIMMIX using the log rank test with the Sidak multiple-comparison adjustment, with the primary outcome as the dependent variable. Differences between groups on secondary outcomes and change over time in implementation measures (e.g., TBRI use) are examined using repeated measures ANOVAs (SAS 9.4, PROC MIXED), with study site as random effects and condition, time, and interactions as fixed factors. Because SU rates are generally lower among JJ females, sex as a biological variable is examined as a moderator of differences in outcomes using univariate analyses (e.g., chi square, t-tests, ANOVA); when significant, tests of moderation are undertaken as part of all analyses. Putative change mechanisms are investigated as mediators of the Group – Primary Outcome relationship and structural equation modeling (SEM; using Mplus) is used to examine sex differences in mediation. For H3, changes in the outcomes over time are examined using repeated measures ANOVAs (SAS 9.4, PROC MIXED), with study site as random effects and time and time × site interactions as fixed factors. For H1–3, a log rank test is used to assess study dropout; stochastic multiple-imputation provides maximum likelihood estimates, accounts for uncertainty in missing values, and provides unbiased estimates of the treatment effect if data are missing at random.

Qualitative data from focus groups are transcribed and qualitatively coded (in Atlas.ti) by at least 2 research staff. An iterative process of coding and thematic analysis [84] are used to understand routine practices employed, nuances in the use of trauma-informed and child-centered strategies, facility facilitators/barriers to uptake of new interventions, general penetration of TBRI within the facility, and facility interest in sustaining and/or expanding TBRI practices.

To address H4 regarding economic components, an activity-based micro-costing approach is used to identify, measure, and value resources invested by participating sites, and link costs to primary and secondary study outcomes [85]. Cost comparisons represent the incremental costs of adopting SRP + TBRI relative to SRP alone. Incremental cost represents the difference in facility/provider cost after adopting the intervention vs before adopting [86, 87], and incremental effectiveness is the difference in time to opioid use initiation in TBRI relative to SRP (and between TBRI support conditions). For each facility, differences in costs and incremental cost-effectiveness ratios are estimated using multi-level general linear models (e.g., generalized linear mixed models) to account for clustering at the facility/provider and patient levels. Nonparametric bootstrapping is used to compute confidence intervals [88].

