#### Randomization

Dyads are randomly assigned to TBRI support condition by the research project director using urn randomization until the recruitment target is met (minimum of 80 per arm; an average of nine per arm, per site). Urn randomization is used to balance the characteristics of youth by group on sex (male vs. female), race (Caucasian vs. other race), and primary speaking language (English vs. Spanish).

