*Public health and safety outcomes* include opioid-related health, opioid use overdose, use of other illegal substances, recidivism, and SU or MH treatment records. *Opioid-related health* outcomes include SU treatment, hospital visits related to SU, diagnosis, overdose, and receipt of Narcan [65]. *Recidivism* information (re-arrest, re-adjudication), urinalysis results, and *treatment* records (type of referral, service receipt) come from JJ facility youth records [65]. For these data, sharing agreements between each state-level JJ facility and the research institute are established, specifying how de-identified records are shared, stored, and analyzed, following models from previous collaborations [66]. *Background information* on youth is extracted from existing JJ youth records (e.g., offense, disposition decision, supervision level, offense history including truancy, and prior SU or MH diagnosis).

Youth and caregivers provide different pieces of background information that serve as covariates or moderators, including demographics (e.g., age, sex, race/ethnicity, employment, education). Caregivers are also asked about their SU (TCU DS 5-OS) [52] and relationship with their own caregiver using the Experiences in Close Relationships-Relationship Structures (ECR-RS) [63]. Other potential covariates include number and type of ACEs [67], youth self-reported social exposure to substance use (e.g., “How often does the adult who is most important to you drink alcohol?”) [53], services youth and family received (adapted from the Child and Adolescent Services Assessment) [68], caregiver motivation in treatment participation (Parent Motivation Inventory; PMI) [69], parenting strain (Caregiver Strain Questionnaire-Revised Short Form; CGSQ-SF) [70], and parental resiliency (Resiliency of Self-Efficacy Scale; RS) [71]. Participants are also asked to respond to two open-ended questions regarding the impact of COVID-19 (e.g., “How is the COVID-19 crisis affecting you or has affected you?”). *Monthly phone check-ins* with youth assess 8 indicators of any opioid use; any alcohol, other drug use; truancy; trouble with the law, increases in depression, increases in anxiety, increases in the stress in relationship with the safe adult in the past month.

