#### Power

For H1 examining the effectiveness of SRP + TBRI compared to SRP alone, the proposed Intent to Treat (ITT) sample will include 360 youth/safe adult dyads (120 SRP, 240 TBRI), with 80 randomized to each TBRI condition. SAS PROC POWER for rank tests comparing 2 survival curves found that, if overall opioid initiation rates are 35% (SRP) vs. 25% (all TBRI groups) at any assessed time point, power is estimated to be at 93% (*α* = .05). For H2 comparing the 3 TBRI conditions, SAS PROC POWER for rank tests comparing 2 survival curves found that for sample sizes of 80 in each group, power = .80 when the hazard ratio = 1.57. When the combined TBRI groups are tested against SRP, power = .80 when the hazard ratio = 1.37.

For H3 and H4 pertinent to the organizational TBRI intervention, the expected sample (nine sites, up to 90 staff participants per site) and the response rate of 25% gives an expected sample of 203 participants. A small effect size (0.20), a power of 0.80, significance level of 0.05, and an intraclass correlation of 0.10 are used to calculate the minimum required sample size. Repeated measures design comparing staff participants over time results in a minimum sample size of 43 participants. To be more conservative, the same parameters are used for a mixed-effect design (four repeated measures by nine sites), yielding a minimum sample size of 189 participants.

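### The log-rank test named for the randomised H2 comparison is valid, but it uses neither the balancing factors nor baseline substance use and so gives up a modest, cheaply recovered amount of power

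*Protocol article*

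**What the plan says.** The protocol's data analysis plan states that for H1 and H2 "comparisons of survival curves for each group are performed using SAS PROC PHREG and PROC GLIMMIX using the log rank test", and that this is done "using the log rank test with the Sidak multiple-comparison adjustment". No strata and no covariates are listed for this test. The next sentence of the same section does list model terms, but for the secondary outcomes: site as random, with condition, time and their interactions as fixed.

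The design section on the effectiveness trial allocates dyads to the three support formats with equal probability within each site. Under Randomization, "Urn randomization is used to balance the characteristics of youth by group on sex (male vs. female), race (Caucasian vs. other race"; primary language (English or Spanish) is the third factor.

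Two other places bear on prognosis. The data analysis plan gives a reason for looking at sex, "Because SU rates are generally lower among JJ females", but uses sex only as a possible moderator, and only if a univariate screen is significant. Measurement and outcomes says that youth and caregivers "provide different pieces of background information that serve as covariates or moderators", without tying any covariate to the H2 test. Table 4 shows that the TCU DS 5-OS and the HEAL substance-use items are completed by youth at baseline.

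**The concern.** H2 compares arms that the randomisation deliberately makes alike on sex, race and language. If those factors predict opioid initiation, a test that ignores them leaves their variation in the comparison, and some of the precision that the balance could provide is lost. The same holds for baseline substance use, which is plausibly the strongest predictor on hand and is already collected. As the text stands, sex can enter only through a data-dependent moderation screen, and the other factors do not enter the named test at all.

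At stake is efficiency, together with a clear prior choice of covariates. The point does not touch the before-after comparison in H1.

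**Working it through.** **The plan's own figure.** The Power section says that "for sample sizes of 80 in each group, power = .80 when the hazard ratio = 1.57". Alpha .05 is stated for H1; it is assumed here for H2, two-sided.
- Events needed (Schoenfeld, 1:1): 4 × (1.960 + 0.842)² / (ln 1.57)² = 4 × 7.85 / 0.2035, or 155. Freedman's formula gives 160.
- Power = Φ(ln 1.57 × √(events/4) − 1.960). With 160 events this is Φ(2.853 − 1.960) = 0.814, so the stated 0.80 is reproduced only if nearly all 160 youth in a pairwise comparison have an event.
- The same section assumes other rates for H1: "if overall opioid initiation rates are 35% (SRP) vs. 25% (all TBRI groups) at any assessed time point". At 25%, 160 youth give 40 events and power is Φ(1.426 − 1.960) = 0.30. At a Sidak level for three comparisons, 1 − 0.95^(1/3) = 0.0170 (the number of comparisons is assumed), it is 0.17.

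The gain from adjustment therefore has to be judged at 25 to 35% events, not with an event in every youth.

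**Simulation at about 25% events.** Three arms and 240 youth were allocated by an urn on three binary factors, and one pairwise comparison was tested at nominal two-sided .05 (not the Sidak level), with exponential times and 5,000 runs per setting. Assumed prevalences: 25% for sex, 50% for race, 20% for language, 50% for a binary baseline substance-use (SU) indicator. Site effects and dropout were not simulated. All tests were run on the same data, and 1.57 is the hazard ratio at fixed covariate values. Monte Carlo standard error is about 0.3 points under the null and 0.7 points for power. The last four columns give power at HR 1.57.

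| Assumed prognostic HRs (sex, race, language; SU) | Mean events, null / HR 1.57 | Type I error, unadjusted | Unadjusted log-rank | Log-rank stratified by urn factors | Cox, urn factors | Cox, urn factors + SU |
|---|---|---|---|---|---|---|
| None | 40.3 / 49.3 | 4.9% | 34.4% | 32.9% | 33.7% | 33.8% |
| 0.50, 1.5, 0.66; none | 41.6 / 50.6 | 4.9% | 34.7% | 35.4% | 35.4% | 35.8% |
| 0.33, 2.0, 0.50; none | 43.9 / 52.8 | 4.5% | 32.3% | 35.7% | 36.0% | 36.0% |
| 0.50, 1.5, 0.66; 2 | 42.5 / 51.6 | 5.2% | 33.0% | 33.3% | 33.5% | 35.0% |
| 0.50, 2.0, 0.50; 4 | 40.6 / 48.4 | 4.4% | 27.6% | 29.4% | 29.0% | 33.4% |

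The closed form at 48 events gives 0.346, in line with the first row.

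Reading the table:
- **Urn factors alone:** the Cox gain is −0.7, 0.7, 3.7, 0.5 and 1.4 points.
- **Urn factors plus baseline SU:** the gain in the last two rows is 2.0 and 5.8 points.
- **No prognostic effect:** adjustment costs 0.6 to 1.5 points.

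**A graded severity score.** A second set of runs (80 vs 80, exact balance within cells, 3,000 runs; 25% female, 40% Caucasian and 15% Spanish-speaking assumed) used a standardised baseline severity score.
- Urn factors only, HR 1.57, 25% events: 28.1% to 29.7%, a gain of 1.6 points.
- Severity HR 2 per SD, HR 1.57, 25% events: 23.5% to 29.0%, a gain of 5.5 points.
- Severity HR 2 per SD, HR 1.57, 35% events: 30.7% to 39.4%, a gain of 8.7 points.
- Severity HR 2 per SD, HR 2.12, 35% events: 70.5% to 79.3%, a gain of 8.8 points.

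**The case against.** The strongest objection is that the protocol never calls the test unadjusted. PROC PHREG and PROC GLIMMIX both accept covariates, background data are said to serve as covariates or moderators, and a condensed article may leave the list to an analysis plan that is not shown. This stands in part: the absence of adjustment is inferred from the named test. But the section does name a test, a log-rank test takes no covariates unless it is stratified, and model terms are given one sentence later for the secondary outcomes. So the point rests on what is written.

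A second objection is that an unadjusted log-rank test after balanced randomisation is valid, so adjustment is a choice for efficiency. That is correct, and the point is put no higher.

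Three stronger readings are tempting and are not supported:
- **That the stated 80% power is missed for this reason.** The Power section concerns a rank test of two survival curves, so its 1.57 is a marginal hazard ratio. With an event in every youth and prognostic urn factors (sex HR 2, race and language 1.5), log-rank power is 71% if 1.57 is the conditional ratio but 82% if it is the marginal one. The marginal ratio being nearer 1 is non-collapsibility, not an error.
- **That the test is clearly conservative.** A type I error of 3.4 to 3.8% appears only when every youth has an event, which conflicts with the assumed 25%.
- **That a linear-model variance reduction of 1 − ρ² with ρ = 0.5 measures the gain.** That formula does not carry over to a Cox model, and the protocol gives no correlation.

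**Conclusion.** The point holds as a modest one about efficiency. The H2 test as written controls its error rate, with type I error of about 4 to 5% at 25% events. It leaves unused information that the design balances on or already collects. At 25 to 35% events, the urn factors are worth about 0 to 3 points of power, with 3.7 points in the most extreme setting tried. Baseline substance use raises the total to as much as about 9 points if it is strongly prognostic (HR 2 per SD). In that case most of the gain comes from baseline substance use. If none of the factors is prognostic, there is nothing to gain and about a point to lose.

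All prognostic strengths and prevalences are assumptions; the protocol says only that substance use is generally lower among females. Adjustment also does not repair the low H2 power at these event rates, about 0.30 with 40 events. That is a separate matter.

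**What to change.** In the data analysis plan, state that the primary H2 analysis is a Cox model in PROC PHREG, which is already named, with these terms:
- condition;
- sex, race (Caucasian or other) and language (English or Spanish);
- one prespecified baseline substance-use score, for example from the TCU DS 5-OS;
- site, either as a stratum or as a random effect, chosen in advance, because allocation is within site.

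Keep the Sidak adjustment for the comparisons between conditions, report the adjusted hazard ratio, and keep the unadjusted log-rank test as a sensitivity analysis. Prespecify that language is dropped if its events are too sparse: with an assumed 15% Spanish-speaking and 25% initiation, 240 × 0.15 × 0.25 = 9 events would carry that term. Say also that the covariates in Measurement and outcomes enter H2 only as listed here.

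The cost is wording and a few model terms, with no new data or participants. The hazard ratio becomes conditional rather than marginal, and up to four degrees of freedom go to the covariates, against about 240 × 0.25 = 60 events over the three arms. Stratifying by site spreads those events over nine strata, about 60 / 9 = 6.7 each, which is a reason to consider the random effect; neither option was simulated.

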## Methods/design

### Research aims

The specific aims of the LeSA Project are to: (1) test the effectiveness of the TBRI intervention and its different support formats – no in-home TBRI support, Structured Coaching, Responsive Coaching – on (a) preventing initiation and/or escalation of opioid use, (b) public health and public safety outcomes, (c) putative change mechanisms, including self-regulation, psychosocial functioning, and relationship with a safe adult; (2) document factors related to TBRI implementation and sustainment; and (3) estimate the start-up and implementation costs and cost-effectiveness of TBRI support options relative to standard re-entry practices in achieving lower rates of opioid initiation and reductions in healthcare and JJ system costs.

Primary hypotheses are as follows:
H1: Compared to youth receiving Standard Re-entry Practices (SRP) only, youth receiving TBRI in addition to SRP are less likely to initiate opioid use following discharge.H2: Compared to no in-home TBRI support, youth receiving Structured or Responsive Coaching are less likely to initiate opioid use following discharge, with the longest time to initiation occurring among youth receiving Responsive Coaching.H3: TBRI is most effective for preventing opioid initiation when facilities routinely use TBRI strategies within their residential settings, given increases in continuity as the youth transitions home from residential care.H4: The cost of implementing TBRI + SRP is higher than SRP alone, with higher cost-effectiveness when TBRI is added.

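### H2's Sidak-adjusted log-rank tests, if single-step, carry a larger penalty than three arms need; a step-down version raises power at no cost in error control

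*Protocol article*

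**What the plan says.** Research aims (Protocol article) lists H2 among the primary hypotheses. It has two parts. First: "Compared to no in-home TBRI support, youth receiving Structured or Responsive Coaching are less likely to initiate opioid use following discharge". Second, within the same sentence: "with the longest time to initiation occurring among youth receiving Responsive Coaching". The predicted order of time to initiation is therefore none, then Structured, then Responsive.

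The Data analysis plan states the method for H1 and H2 together: "comparisons of survival curves for each group are performed using SAS PROC PHREG and PROC GLIMMIX". The test and its multiplicity correction are named next: "using the log rank test with the Sidak multiple-comparison adjustment". It does not list the comparisons, the size of the family, or whether the adjustment is single-step or step-down.

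The Power section treats H2 as two-curve tests: "For H2 comparing the 3 TBRI conditions, SAS PROC POWER for rank tests comparing 2 survival curves found", for 80 per group, "power = .80 when the hazard ratio = 1.57". The allocation is given as "with 80 randomized to each TBRI condition".

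**The concern.** H2 compares the three support formats, which is the trial's only randomised comparison. At the Power section's 25% initiation rate for the TBRI groups, the three arms yield about 240 × 0.25 = 60 events, so any avoidable loss of power matters.

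The Sidak wording, read with the two-curve power basis, points to a single-step adjustment over three pairs. That charges every pair the full three-test penalty even after one difference has been established. With three groups the penalty is no longer needed at that point, because the three equalities are logically linked. What is at stake is H2's first part, that both coaching formats beat no support. It needs two rejections, and the second is where single-step Sidak is needlessly strict.

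**Working it through.** **Inputs.** From the Power section: 80 per arm; 25% initiation over the TBRI groups; hazard ratio 1.57 for power 0.80; alpha 0.05 (stated with H1, two-sided assumed). Assumed: the individual arm rates (each set averages 25%), exponential times, censoring at a common horizon, and a family of three pairs.

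**1. The plan's own H2 figure.** Schoenfeld, equal arms: power = Φ(√(d/4) × ln HR − z).
- d = 160 (every youth in a pair initiates), z = 1.960: √40 × 0.451 = 2.853; 2.853 − 1.960 = 0.893; power 0.814. This matches the stated 0.80 to within 2 points.
- The match needs an unadjusted alpha. Sidak for three pairs is 1 − 0.95^(1/3) = 0.01695, z = 2.388: 2.853 − 2.388 = 0.465; power 0.68.
- At 25% initiation, d = 160 × 0.25 = 40 per pair: √10 × 0.451 = 1.426. Power is 0.30 unadjusted and 0.17 with Sidak.

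So the Sidak penalty matters, and the event count matters more.

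**2. Why 0.05 is enough after the first rejection.** The null hypotheses are none = Structured, none = Responsive and Structured = Responsive. Any two imply the third, so the number of true nulls is three, one or zero, never two.
- All three true: an error requires the smallest p-value to pass 0.017, so the familywise rate is the same as for single-step Sidak.
- Exactly one true: an error requires that one pair to reject at no more than 0.05, so the rate is at most 5%.

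The step-down rule rejects everything single-step Sidak rejects, because any pair below 0.017 is also below 0.05 and the first step has then passed.

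**3. Simulated power to show both coaching arms beat none (80 per arm).**

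| None/Structured/Responsive | Single-step | Step-down | Gain |
|---|---|---|---|
| 33/25/17% | 8% | 16% | 8 points |
| 35/25/15% | 14% | 26% | 12 points |
| 35/20/20% | 23% | 36% | 13 points |

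A second set of runs agrees to within 2 points. At 33/25/17%, Structured versus none rises from 9% to 16%, but Responsive versus none only from 47% to 49%. It is usually the pair with the smallest p-value, so it faces 0.017 under either rule.

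**4. Error check.** With equal rates, any rejection occurred in 3.5% of runs. With one true-null pair, that pair was rejected in at most 4.7%. Both agree with the nominal 5%, subject to the log-rank test's large-sample approximation.

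**5. If H1 is in the same family.** Rejecting the SRP comparison says nothing about equality of the three TBRI arms: all three H2 nulls could still be true. Testing them at 0.05 each would then not control familywise error, so the shortcut in step 2 fails.

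**The case against.** The strongest defence is that the article does not state all pairs, single-step or 0.017, and that a condensed article may leave these details to the full protocol or SAP. This stands: the point depends on the default reading. If only the two coaching-versus-none pairs were meant, Sidak gives 1 − 0.95^(1/2) = 0.0253 each and the penalty is smaller. It is also true that Sidak-adjusted log-rank tests control familywise error and answer H2's component statements directly. Nothing in the plan is invalid here.

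A reader might infer more: that because H2 is ordered, unordered tests are wrong and an ordered (trend) log-rank should come first as a gate. The documents do not support that. A trend test does gain under evenly spaced rates (85% against 75% for any Sidak pair at 35/25/15%), but it fails when the order is wrong. At 33/17/25% the chance of rejecting any pair falls from 53% to 23% with a trend gate; at 35/15/35% it falls from 85% to 7%. A best result for Structured is not far-fetched: Table 3 requires four coaching modules for Structured and two for Responsive, the rest being optional, so the arms are not increasing doses.

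A reader might also infer that Sidak is why the full ordering will almost never be shown. At 33/25/17% all three pairs reject in about 0.2% of runs under Sidak, and in only 1.1% when each pair is tested at 0.05 after a significant trend. Step-down also asks every pair to reach 0.05, so it is limited in the same way. The cause is few events and 80 per arm.

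**Conclusion.** The point holds as an inefficiency, not an error. Read as single-step over three pairs, the adjustment is stricter than needed, and step-down Sidak is uniformly at least as powerful with the same familywise guarantee. The gain is about 8 to 13 points for showing that both coaching arms beat none, and about 2 points for Responsive versus none in the two evenly ordered scenarios. Even after the change, power for the two-arm claim is only 16% to 36% in these scenarios.

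This rests on the inferred family of three pairs, two-sided tests and the assumed arm rates; only their 25% average comes from the document.

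**What to change.** - State that the three pairwise comparisons among TBRI support arms form their own family, separate from the H1 comparison with SRP.
- Use step-down Sidak: test the pair with the smallest p-value at 0.017; if it rejects, test the other two at 0.05 each; otherwise stop.
- If H1 and H2 stay in one family of m tests, use ordinary Holm-Sidak instead: the j-th smallest p-value is tested at 1 − 0.95^(1/(m − j + 1)), stopping at the first non-rejection.
- Claim that Responsive gives the longest time to initiation only if Responsive versus Structured rejects in Responsive's favour.
- A trend log-rank may be reported as supportive, but should not gate the pairwise tests.

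The cost is analysis-plan wording only, with no extra participants or data. The one small loss is that step-down tests have no matching simultaneous confidence intervals, so the plan should say which intervals will accompany the estimates.

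### The plan powers H1 as one pooled test at alpha .05 but analyses H1 and H2 under a Sidak adjustment with no stated family, so the H1 threshold is not fixed and the H2 power ignores the adjustment.

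*Protocol article*

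**What the plan says.** In the protocol article, Research aims, H1 is a single contrast against SRP alone: "youth receiving TBRI in addition to SRP are less likely to initiate opioid use following discharge". H2 compares the three TBRI support formats with one another.

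The Power section follows that structure. The sample is "360 youth/safe adult dyads (120 SRP, 240 TBRI), with 80 randomized to each TBRI condition". For H1 it assumes "if overall opioid initiation rates are 35% (SRP) vs. 25% (all TBRI groups) at any assessed time point", and the result is "power is estimated to be at 93% (*α* = .05", with no multiplicity adjustment mentioned. It adds for the same pooled contrast: "When the combined TBRI groups are tested against SRP, power = .80 when the hazard ratio = 1.37". For H2 it says that "for sample sizes of 80 in each group, power = .80 when the hazard ratio = 1.57", again without an adjustment.

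The Data analysis plan gives one rule for both hypotheses: "For H1 and H2, comparisons of survival curves for each group are performed", and this is done "using the log rank test with the Sidak multiple-comparison adjustment, with the primary outcome as the dependent variable". The number of comparisons is not given. Nor does the text say whether H1 and H2 form one family or two.

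**The concern.** The analysis sentence names H1 as covered by the Sidak adjustment, while the Power section treats H1 as one test at .05. A Sidak adjustment of a single comparison changes nothing, so a reader may well take the sentence to place H1 in a set with the H2 comparisons. Its threshold would then be smaller than the one used in planning.

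H1 is the main effectiveness claim. If the family is still open when the H1 p-value is known, a p-value somewhat below .05 can be called significant or not by choosing the reading afterwards. For H2 there are several comparisons on any reading, so the adjustment applies, yet the stated detectable hazard ratio appears to have been computed without it.

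**Working it through.** **Inputs.** From the Power section: 120 SRP and 240 TBRI dyads, 80 per TBRI condition, alpha .05 (stated for H1), 80% power at hazard ratio (HR) 1.37 for the pooled contrast and at 1.57 for two groups of 80. From the Data analysis plan: log-rank test and Sidak adjustment. Not stated, and therefore assumed: two-sided testing and the number k of comparisons in the family.

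**Formulas.** Log-rank power by the Schoenfeld approximation: Φ(ln HR × √(D·p·(1−p)) − z), where D is the number of events, p the share of dyads in one group and z the two-sided critical value. Sidak threshold per comparison: 1 − .95^(1/k).

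**Step 1: reproduce the plan's figures.** They come back when every participant is counted as an event.

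- H1, HR 1.37: ln 1.37 × √(360 × 1/3 × 2/3) = .3148 × 8.944 = 2.816. Then Φ(2.816 − 1.960) = .804.
- H2, HR 1.57: ln 1.57 × √(160 × 1/4) = .4511 × 6.325 = 2.853. Then Φ(2.853 − 1.960) = .814.

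Both match the stated .80. One-sided .05 gives .879 and .886. Two-sided Sidak with k = 3 gives .666 and .679. Of the settings checked, only the unadjusted two-sided .05 fits both figures, so the planning appears to have used no adjustment.

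**Step 2: H1 under each possible family (360 events, HR 1.37).**

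| Assumed k | Threshold | z | Power |
|---|---|---|---|
| 1 (Sidak within H1 only) | .0500 | 1.960 | .804 |
| 2 | .0253 | 2.236 | .719 |
| 3 | .0170 | 2.388 | .666 |
| 4 (pooled H1 plus three H2 pairs) | .0127 | 2.491 | .627 |

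If the stated 93% is taken at face value instead, it becomes 88%, 85% and 83% for k = 2, 3 and 4.

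**Step 3: H2 with its own adjustment (160 events, HR 1.57).** Three support conditions give three pairs, so k = 3 and the threshold is .0170. Power is Φ(2.853 − 2.388) = .679. The HR with 80% power is exp((2.388 + .842)/6.325) = 1.67, against the stated 1.57. If only two comparisons were meant, the threshold is .0253 and power is Φ(2.853 − 2.236) = .731. If H1 shares the family (k = 4), power is Φ(2.853 − 2.491) = .641.

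**The case against.** The strongest reply is that no contradiction is proven. Sidak can be applied within each hypothesis. H1 is then one comparison, its threshold is 1 − .95 = .05, and the two sections agree. Research aims, Overall study design, Power and the cost-effectiveness paragraph of the Data analysis plan all fit H1 as TBRI against SRP. The alpha in a power calculation is also an input and not itself a decision rule, and a condensed article may leave the family to a fuller document. A joint Sidak family over H1 and H2 would be a valid, more conservative choice.

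Much of this stands, and it rules out stronger readings that a reader might infer:

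- That a given H1 p-value is both positive and negative under the plan. The within-hypothesis reading leaves H1 at .05, so the verdict is undetermined, not contradictory.
- That the H1 threshold is some particular small value such as .0127, or .0085 for all six pairs of the four groups. No count is in the document, and the six pairs do not contain the pooled contrast that H1 states.
- That about 20 percentage points of results at the planned effect hang on the choice. That size needs the stated 93% to be replaced by the roughly 49% that follows from 35% against 25% with 102 events. Whether the 93% is right is a separate question.

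The reply does not dispose of the point. The sentence names H1 under the adjustment and does not confine Sidak to a single hypothesis. The within-hypothesis reading that rescues H1 also confirms that the adjustment applies to H2, where the stated power leaves it out. That is a mismatch between two stated rules and not merely detail left to another document.

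**Conclusion.** The point holds in a limited form. The document does not fix the threshold for H1: it is .05 if Sidak is applied within each hypothesis, and .025, .017 or .013 if H1 shares a family of two, three or four comparisons. On the shared readings the stated 80% at HR 1.37 would be about 72%, 67% or 63%. An H1 p-value between the adjusted threshold and .05 has no determined verdict.

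For H2 the mismatch remains on either reading: .80 at HR 1.57 becomes about .68 with three pairs at .017 each.

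These sizes assume two-sided tests and the listed values of k. They also keep the plan's apparent event count, in which every participant has an event, so that only the threshold changes. They show the cost of the adjustment and do not endorse that event count.

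**What to change.** In the Data analysis plan, state that H1 is tested by one pooled contrast, all SRP + TBRI dyads against SRP, at two-sided alpha .05. State that the Sidak adjustment applies only to the H2 comparisons among the TBRI support conditions, and give their number (three pairs, .017 each). In the Power section, restate the H2 power or detectable hazard ratio at that adjusted level. With the present event count this is about .68 at HR 1.57, or 80% at about HR 1.67.

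This matches how H1 is already hypothesised and powered. It needs a few sentences and should be settled before outcomes by group are seen. There are three costs. Separate comparisons of each TBRI condition with SRP become descriptive. Error is controlled within each hypothesis and not jointly over H1 and H2. The stated H2 power becomes less favourable.
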